### Data collection and handling

All relevant information will be collected using a case report form (CRF). Double data input will be used for the data entry, and will be checked at the second input. The QMB and the principal investigator will check and examine the data, which will then be secured and sent to the statistician.

### Ethical issues

The final study protocol and the final of written informed consent form were approved by the Biological and Medical Ethics Committee (BMEC) of West China Hospital (2012 Reviewed-No.114). Good Clinical Practice and ethical principles described in the Declaration of Helsinki will be strictly adhered to guarantee patient rights. The trial will be carried out in keeping with local laws and regulations. Full disclosure will be given to the person responsible for the patient. The information will be given before the person responsible agrees to participate in this trial and signs the informed consent, and will include the natural history of SAH, the treatment procedure, risks, possible consequences and the costs of PGASAH. Patients can be withdrawn from the trial for any reason and at any time.

### Adverse and severe adverse events

Adverse events (AE) are defined as any unwanted incidents in patients during the trial. Coma was excluded as an AE, because all patients enrolled in the trial were in poor neurological condition on admission. Serious adverse events (SAE) are defined as death or vegetative state. Both AEs and SAEs will be recorded on the CRF, including the details of the event, the correlation with the trial, the start and the end date, treatments used, their efficacy and outcomes. In the case of AEs and SAEs, the BMEC and QMB will be informed within 24 hours after the SAEs are detected .

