However, some flaws existed in the ISAT study. First, optimal timing of surgery may not have been considered, because a 14 hours lapse in the intervention timing of the two treatments. Second, the study excluded more cases that were suitable for neurosurgical clipping. Third, the study didn’t include middle cerebral aneurysms. Fourth, long-term follow-up outcomes were unknown. Fifth, The ISAT study ignored a selection bias, with major surgical intervention centers in the United States and Japan being excluded [10]. Furthermore, the ISAT Collaborative Group distinctly known that the number of patients younger than 40 years or older than 70 years was small, no consistent trend for age was observed. And a limited number of patients with PGASAH were enrolled in the ISAT study [9]. So, the conclusion that patients with aSAH who received endovascular coiling showed a better clinical outcome than those received neurosurgical clipping should be suspected.

The timing of surgical intervention for SAH has been debated worldwide. Pros and cons exist for patients with PGASAH who received different timing of surgery. PGASAH patients are more prone to encounter rebleeding than patients in good clinical condition [11-14]. Early surgery can secure the aneurysm neck to avoid rebleeding which would cause irreparable outcomes, and reduce disability rate and mortality [6]. If the patient receives early surgery, triple-H therapy can be performed as soon as possible to avoid vasospasm postoperatively [14,15]. However, in early surgery, serious cerebral edema may cause brain injury, postoperative hemorrhage, difficult exposure of the aneurysm intraoperatively and other operative complications [16]. The advantages of delayed surgery include the less brain swelling and less cerebrovascular instability during the surgery. Decline in operative mortality have been associated with the operation that is relatively easy. However, the aneurysm may rupture again if surgery is delayed, thus increasing mortality [17].

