### Blinding

Because of the nature of the study, only the observer can be blinded. In order to prevent bias, the following measures will be taken. 1) Patient characteristics will be collected and evaluated by two special doctors who are not involved in any other stage of the trial. 2) Patient randomization will be performed by an independent random analyst. 3) Patient outcomes will be followed up by two special investigators who are not involved in the allocation or the treatment process. 4) Statistical analysis will be performed by a special statistician who did not participate in the implementation of the study. 5) Because of the sequence of the Case Report Form (CRF), each stage of the study will be completed in a specific order by the allocated individuals. Patient characteristics will be the first section completed, followed by the independent random analyst, subsequently the neurosurgeons will describe the treatment procedure, complications, adverse and severe adverse events in the CRF, the last will be the two special investigators. All the researchers will submit a copy of their original data to the Quality Monitoring Board (QMB), before the CRF is available.

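### The two-state definition of a serious adverse event leaves non-fatal rebleeding and other grave events without a clear 24-hour report, and the unqualified coma exclusion drops later decline that shows only as coma

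*Protocol article*

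**What the plan says.** The section Adverse and severe adverse events sets four rules:

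- The adverse event category is broad: "Adverse events (AE) are defined as any unwanted incidents in patients during the trial".
- One state is taken out of it: "Coma was excluded as an AE, because all patients enrolled in the trial were in poor neurological condition on admission".
- The serious category is closed: "Serious adverse events (SAE) are defined as death or vegetative state".
- On handling, "Both AEs and SAEs will be recorded on the CRF", with details, relation to the trial, dates, treatment and outcome. On notification, "the BMEC and QMB will be informed within 24 hours after the SAEs are detected". That last sentence opens by naming both adverse and serious adverse events, but ties the clock to the serious ones.

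Other sections bear on this. Under Ethical issues, "Good Clinical Practice and ethical principles described in the Declaration of Helsinki will be strictly adhered to guarantee patient rights". Under Blinding, "subsequently the neurosurgeons will describe the treatment procedure, complications, adverse and severe adverse events in the CRF". Withdrawal from the study lets a patient be withdrawn for personal safety when severe adverse events occur. On the risk of waiting, the Background says: "However, the aneurysm may rupture again if surgery is delayed, thus increasing mortality".

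**The concern.** A seriousness definition decides which events reach the oversight bodies quickly. Here it admits only the two worst end states. Events that threaten life or leave lasting disability, but do not end in death or vegetative state, fall below the line. In this trial they include the non-fatal form of the very hazards that the Background weighs against each other: re-rupture while waiting, and hemorrhage or brain injury from operating early.

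The coma exclusion adds a second gap. Its stated reason is the patients' condition on admission. That reason covers coma already present at baseline, but the rule as written covers coma at any time.

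At stake are timely safety oversight in a trial of critically ill patients, and the completeness of the adverse event record for neurological decline. The efficacy analysis is not affected.

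**Working it through.** No arithmetic applies, because the point depends on no sample size, power or event figure. The check applies the stated definitions to each type of event and then compares the sections.

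**Step 1. Classify the events.**

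| Event after enrolment | Serious adverse event? | On the CRF as an adverse event? | 24-hour notice? |
|---|---|---|---|
| Fatal rebleed | Yes | Yes, as serious | Yes |
| Any event ending in vegetative state | Yes | Yes, as serious | Yes |
| Non-fatal rebleed, no vegetative state | No | Yes | Not clearly |
| Non-fatal postoperative hemorrhage or disabling infarct | No | Yes | Not clearly |
| Decline showing only as deeper or recurrent coma | No | No, excluded | No |

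The entry is *not clearly* rather than *no* because the reporting sentence starts with both categories and then names only one as the trigger.

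**Step 2. Compare with Ethical issues.** The article promises strict adherence to Good Clinical Practice. It does not spell out the seriousness criteria, but a two-item list that omits life-threatening and disabling events is hard to square with that promise.

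**Step 3. Compare with Withdrawal from the study.** That section, the Blinding section and the heading of the adverse event section say *severe*; the definition says *serious*. There are two readings:

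- If the terms mean the same, withdrawal for personal safety is open only after death or vegetative state, which makes little sense.
- If they differ, *severe* is undefined.

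Either way the two sections need to be reconciled.

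**Step 4. Compare with the Discussion.** It provides for emergency surgery in the intermediate and late groups when, for example, a space-occupying hematoma or midline shift is confirmed. So the protocol expects grave preoperative events that its serious category does not capture.

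**Step 5. Test the reason for the coma exclusion.** Hunt & Hess Grades IV and V are both eligible (Inclusion criteria), and the grade is a stratification factor (Randomization). A baseline grade is therefore on record for every patient, and later worsening can be judged against it. The reason given does not require such worsening to be ignored.

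**The case against.** The strongest reply is that little is actually hidden.

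- **Recording.** A non-fatal rebleed is an unwanted incident, so it is recorded on the CRF as an adverse event, and the neurosurgeons also record complications. This stands. A reader might infer that non-fatal rebleeding escapes the harm counts; it does not. Only decline whose sole recorded sign is coma is lost, and a rebleed that deepens coma is still recorded as a rebleed.
- **Oversight.** Under Blinding, all researchers send copies of their original data to the QMB, and under Data collection and handling the QMB checks the data. This also stands. It would be wrong to say that oversight learns of harm only once patients die or become vegetative. What is missing is a clear prompt notice.
- **Ambiguity.** The reporting sentence can be read as reaching ordinary adverse events too. True, and that ambiguity itself needs correcting.
- **Coma on admission.** The Abstract describes these patients as unconscious on admission, which supports excluding baseline coma and makes first-onset coma a weak example. Deepening coma, or relapse after improvement, remains uncovered.
- **Direction.** A reader might infer that harm is undercounted specifically in the delayed arms. The document does not support this. The Background gives early surgery its own non-fatal hazards, which the same definition omits. The Discussion keeps deaths while awaiting surgery in the analysed results. Lasting disability is measured by the outcome scales listed under Follow-up.
- **Design choice.** A high threshold may be defended in a population in which, according to the Background, more than 60% die or become dependent. That could justify exempting listed expected events from expedited notice. It does not explain a closed definition that conflicts with other sections.

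**Conclusion.** The concern holds in a limited form. The definition of a serious adverse event is stated, and stated too narrowly; this is not detail lost when a protocol is condensed into an article. Non-fatal rebleeding, postoperative hemorrhage and other life-threatening or disabling events short of vegetative state have no clear expedited report, in any arm. Separately, in-trial decline that shows only as deeper or recurrent coma drops out of the adverse event record.

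The size cannot be given. The document states no rate of non-fatal rebleeding in this trial's arms and no allocation ratio for the 99 patients, so any count of unreported events would rest on assumption alone.

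The conclusion rests on two readings: that the 24-hour clock applies to serious adverse events only, which is the natural sense of the sentence, and that the coma exclusion applies throughout the trial, as it is worded. The change should be made for patient safety and consistency. It does not put the primary comparison in doubt.

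**What to change.** Amend the section Adverse and severe adverse events, and the sections that depend on it:

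1. Replace the two-state definition with the standard Good Clinical Practice seriousness criteria, so that life-threatening and disabling events are included and non-fatal rebleeding before or after surgery is reportable.
2. Limit the coma exclusion to coma present at baseline, and record any worsening from the baseline grade as an adverse event.
3. Rewrite the reporting sentence so that it states which events start the 24-hour clock to the BMEC and QMB.
4. Use one term, *serious* or *severe*, or define both, and reconcile the safety withdrawal rule with the definition.

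The cost is amendment wording and more reports for the BMEC and QMB to handle. The sample size, randomisation, timing groups and outcomes are unchanged.

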### Statistical analysis

Intention-to-treat (ITT) analysis and per-protocol (PP) analysis will be performed. The level of significance required for 80% power and a 5% (2-sided) significance level will be used. All data will be analyzed by the statistical analysis using Statistical Package for Social Sciences software (SPSS), version 17.0. Quantitative variables will be analyzed using t-test. Chi-square test and Fisher’s exact test will be used to analyze categorical variables. To analyze the outcome at 6 months after surgery, a comparison between groups will be made using the Mann–Whitney U-test and the significance of observed differences in outcome will be assessed with the Fisher’s exact test. Survival analysis will be further compare mortality between groups. Logistic regression will be used to adjust the effect of multivariable.

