## Background

Subarachnoid hemorrhage (SAH) is a common fetal cerebrovascular disease. Its annual incidence is 2–32 cases per 100,000 population, and contributes to 5% of stroke cases [1,2]. More than 85% of SAH are caused by aneurysms [3]. Poor grade aneurysmal subarachnoid hemorrhage (PGASAH) , is classified as Grade IV and V and accounts for approximately 20-40% of patients with SAH [4]. The prognosis of PGASAH is extraordinarily poor. More than 60% patients will become dependent or will die [5,6]. Without surgical intervention, the mortality rate of PGASAH can reach more than 90% [7].

Neurosurgical clipping and endovascular coiling are considered two main treatments for patients with intracranial aneurysm. Whether patients with aneurysms can benefit from surgery is still controversial, especially for those with PGASAH, which is the most critical subtype of SAH. In 2003, Maurice-Williams RS asserted the history of aneurysm surgery would end with experienced neurosurgeons is draining away as a result of death and retirement [8]. However, the truth of the matter was quite different.

Previous trials have been performed to compare the prognosis of neurosurgical clipping and endovascular coiling. The most significant study is the International Subarachnoid Aneurysm Trial (ISAT) conducted by Molyneux et al. [9]. Two thousand one hundred forty three patients with aSAH were randomly divided into neurosurgical clipping (n = 1070) or endovascular treatment. Outcomes at 1 year indicated that although the rebleeding rate was more common after endovascular coiling than neurosurgical clipping, endovascular coiling resulted in better clinical outcomes.

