### Overview of study design

West China hospital receives the most patients with PGASAH in western of China. This study is a prospective, single-centre, observer-blinded, randomized controlled trial with stratification according to the patient’s age, gender, Hunt & Hess grading and the size of aneurysm. Ninety-nine patients meeting the criteria will be randomly assigned into three treatment groups. The early surgery group will receive operation within 3 days after onset of SAH, the intermediate surgery group from days 4 to 7, and the late surgery group after day 7 post-SAH.

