### Follow-up

Two investigators (senior neurosurgeons) that are not involved in allocation or treatment will follow up of all patients at 1, 3, and 6 months after neurosurgical clipping. Primary outcomes of the trial are the Extended Glasgow Outcome Scale and the Modified Rankin Scale (mRS) at 6 months after aneurysm clipping. Both scales will be measured with structured interviews. The secondary indicators include the Barthel Index and mortality.

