**Figure 1 F1:**
[figure not shown]
The study considerations of our trial.

This trial was elaborately designed to avoid several forms of bias and improve accuracy. The experience of presciously authors was noted and was merged into our design of the trial [19-21]. We will record all treatment results and surgical results, but only treatment results will be utilized for analysis. This will avoid selection bias, because all treatment results will include patients that may die from rebleeding, vasospasm or other complications, when awaiting surgery, especially those patients assigned to the intermediate or late surgery groups. Patients in intermediate or late surgery groups will receive emergency surgery when space-occupying hematoma, midline shift and emergency surgery indications are confirmed. Bias will be solved through the use of ITT analysis.

Although previous reports have demonstrated that patients in poor condition on admission within 6 hours after the onset of SAH achieved better outcomes than patients admitted later [12,26], this trial will enroll all the patients with PGASAH on admitted within 72 hours. As one of the largest hospitals in China, the number of patients admitted within 6 hours after the onset of SAH was relatively small in our department. More patients are transferred from other cities, even from the outlying areas in the west of China, and which takes time. The trial was not designed to include a small number of patients, but to include the overwhelming majority of the patients.

Neurosurgeon experience is an important factor in outcome after SAH. More than 4,000 surgeries are completed in our Department of Neurosurgery every year. Every neurosurgeon participating in the trial has accumulates experience of more than 200 neurosurgical clippings yearly, thus ensuring that every surgery will be performd to a high standard.

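### The t-test is fixed for quantitative variables in a three-arm trial; pairwise use gives about 12% familywise error, and a survivors-only Barthel comparison could favour an arm with more deaths

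*Protocol article*

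**What the plan says.** All references are to the protocol article.

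- **Design (Overview of study design):** "Ninety-nine patients meeting the criteria will be randomly assigned into three treatment groups".
- **Test for quantitative variables (Statistical analysis):** "Quantitative variables will be analyzed using t-test". The section states a two-sided 5% level. It names no three-group test for these variables and no adjustment for multiple comparisons.
- **Test for the 6-month outcome (same section):** "To analyze the outcome at 6 months after surgery, a comparison between groups will be made using the Mann–Whitney U-test". Which outcome or outcomes this covers is not defined.
- **Mortality (same section):** "Survival analysis will be further compare mortality between groups".
- **Barthel Index (Follow-up):** "The secondary indicators include the Barthel Index and mortality". Its variable type, test and primary time point are not given. Visits are at 1, 3 and 6 months, counted from clipping.
- **Prognosis (Background):** "More than 60% patients will become dependent or will die". This is a composite and not a death rate.
- **Deaths before surgery (Discussion, after Figure 1):** "all treatment results will include patients that may die from rebleeding, vasospasm or other complications, when awaiting surgery". The authors expect these deaths mainly in the intermediate and late arms and rely on intention-to-treat analysis to deal with the bias.

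**The concern.** There are two linked problems.

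First, the article states a test that does not fit the design. Comparing three timing groups by t-test means three pairwise tests. With no adjustment, the chance of a false positive for each quantitative variable is well above the stated 5%. This is a rule the article fixes, so it is more than a detail left for an analysis plan.

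Second, the Barthel Index is the named outcome that most resembles a quantitative score, and it has no level for death. GOSE and mRS do have one. The article itself expects deaths to differ by timing: the Background says delay risks re-rupture and higher mortality, and the Discussion expects deaths while patients wait. If only survivors contribute a Barthel score, the groups compared are no longer the randomised groups. An arm that keeps severely disabled patients alive can then show a lower mean than an arm in which they die.

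**Working it through.** **Inputs.** From the article: three arms, 99 patients, two-sided 5%. Equal allocation is assumed, so 99 / 3 = 33 per arm, with loss to follow-up ignored. The article gives no arm-specific mortality and no Barthel mean or SD, so those are assumed below. Its sample-size figure of 88 rests on a binary unfavourable outcome. The only figure of the plan's own that bears on this point is the 5% level.

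**Step 1: familywise error of the stated rule.** Three arms give 3 pairs.

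- If the tests were independent: 1 − 0.95³ = 1 − 0.857 = 14.3%.
- The pairs share arms, so the true figure is lower. Simulation of 40,000 null trials with 33 normal observations per arm: 12.3% have at least one p < 0.05 (simulation standard error about 0.2 points).
- One three-group test at 5% has a 5% error.

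**Step 2: which rule covers Barthel.** The t-test sentence covers quantitative variables in general. The Mann–Whitney sentence refers to the 6-month outcome, and its time point echoes the Follow-up definition of the primary outcomes (GOSE and mRS at 6 months after clipping). Barthel is listed separately, as secondary, with no time point attached. The t-test is therefore the more natural reading, but the Mann–Whitney reading is open. Both tests compare two groups, so the three-arm mismatch remains under either.

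**Step 3: how survivor means can mislead (assumed figures).** Take mortality of 20% versus 40%. Survivors who would live in either arm average 70. The extra 20% saved in the first arm average *x*. The survivor mean in the lower-mortality arm is (0.6 × 70 + 0.2 × *x*) / 0.8, against 70 in the other arm.

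- *x* = 20: 57.5, a gap of 12.5 points against the arm with fewer deaths.
- *x* = 50: 65, a gap of 5 points.
- *x* = 70: no gap.

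The effect depends entirely on how disabled the additional survivors are.

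**Step 4: how often this would be significant.** Two arms of 33 with the same underlying function; score = 50 + 35 × standard normal, rounded to 5s and limited to 0–100. A patient dies when a standard normal risk variable, with correlation ρ to function, falls below the quantile for the arm's mortality. There were 4,000 trials per row. The percentages are trials in which the t-test on survivors significantly favours the arm with **more** deaths.

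| Assumed mortality | ρ = 1 (worst die) | ρ = 0.5 | ρ = 0 (unrelated) |
|---|---|---|---|
| 30% vs 30% | 2.5% | 2.9% | 2.4% |
| 30% vs 40% | 11.0% | 4.7% | 2.3% |
| 30% vs 50% | 31.4% | 6.8% | 2.4% |
| 40% vs 60% | 37.9% | 6.7% | 3.0% |
| 20% vs 50% | 56.6% | 10.8% | 2.6% |

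The nominal level in one direction is 2.5%, so the ρ = 0 column shows essentially no bias. At 30% versus 50%, the mean survivor difference in favour of the arm with more deaths is 9.7 points (ρ = 1), 4.5 (ρ = 0.5) and about 0 (ρ = 0). With death ranked worst and a Mann–Whitney test, the arm with more deaths is significantly favoured in at most 0.4% of trials at 30% versus 50%. The three-arm Kruskal–Wallis version was not simulated.

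**The case against.** The strongest reply is that the article never assigns the Barthel Index to the t-test. The sentence on quantitative variables is generic and could be meant for age, aneurysm size or intracranial pressure. Barthel is collected at the 6-month visit, so the Mann–Whitney sentence can cover it. This stands: the t-test reading of Barthel is an inference.

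Nor does the article say that the dead are dropped. The Discussion means deaths before surgery to count in the analysed results, and a scoring rule for the dead may sit in the full protocol or analysis plan, which are not shown. This also stands, and the silence alone is not a fault. It does not remove the risk: intention-to-treat keeps a patient in the assigned arm but supplies no Barthel value after death, and visits counted from clipping have no starting point for a patient who dies before surgery.

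A reader might infer that the trial as a whole could favour the deadlier timing. The documents do not support that. Barthel is one secondary outcome, mortality is compared separately by survival analysis, and the primary outcomes are GOSE and mRS.

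Finally, ranking death worst answers a question about death and function combined. It is a defensible choice but not the only one.

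None of this answers the three-arm mismatch. That the Mann–Whitney test shares it makes the problem wider than the t-test sentence.

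**Conclusion.** The mismatch between a two-group test and three arms holds as written: about 12% familywise error (12.3% simulated, 14.3% as the independence figure) against the stated 5%, assuming equal arms of 33 and unadjusted pairwise testing.

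The Barthel part holds only conditionally. It needs scores to be compared among survivors, mortality to differ by arm, and death to be linked to poor function. Under assumed mortality of 30% versus 50%, a survivors-only t-test significantly favours the arm with more deaths in 2.4% of trials (no link) to 31% (worst patients die). A larger or smaller mortality gap moves the upper end, as the table shows. No single figure can be fixed from the documents, and quoting only the upper end would overstate the case. The point concerns the Barthel comparison alone. It is worth correcting because the correction is cheap; it does not threaten the design.

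**What to change.** In Statistical analysis:

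1. Replace the t-test for quantitative variables with one three-group test (ANOVA, or Kruskal–Wallis where the distribution is skewed or bounded). Make pairwise comparisons only if that test is significant. With exactly three groups this keeps the familywise error at about 5%: if all three arms are equal, the first test limits the error, and if only two are equal, one true null comparison remains.
2. Name the Barthel analysis: score at 6 months, all randomised patients, death ranked below the lowest score, Kruskal–Wallis across the three arms. Report survivor-only means as descriptive.

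The cost is about two sentences, with no change to design, data collection or sample size. The small downside is that the Barthel result becomes a rank measure combining death and function, which is harder to read than a mean difference. The descriptive survivor means and the separate mortality analysis help the reader take the two apart.

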### Sample size

The rate of unfavorable outcomes in patients with PGASAH is approximately 50% [22]. A statistically significant difference in unfavorable outcomes between the different surgery times is 30%, which would have statistically significant differences. A sample size of 88 will be required with 80% power and a 5% (2-sided) significance level. On consideration of the loss to follow-up, the sample size will be increased to 99 subjects.

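### A two-sample test for three arms and two unranked primary scales leave the 5% level uncontrolled: about 12% on one scale, roughly 15–20% if either scale suffices (correlation assumed)

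*Protocol article*

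**What the plan says.** Under Overview of study design: "Ninety-nine patients meeting the criteria will be randomly assigned into three treatment groups" (early, intermediate and late surgery).

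Under Follow-up: "Primary outcomes of the trial are the Extended Glasgow Outcome Scale and the Modified Rankin Scale (mRS) at 6 months after aneurysm clipping". The section does not say whether one scale or both must show a difference, or which takes precedence.

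Under Statistical analysis, the 6-month result is handled in one sentence with two tests. First, "To analyze the outcome at 6 months after surgery, a comparison between groups will be made using the Mann–Whitney U-test"; then, "the significance of observed differences in outcome will be assessed with the Fisher’s exact test". The same section sets the level once: "a 5% (2-sided) significance level will be used". It opens with "Intention-to-treat (ITT) analysis and per-protocol (PP) analysis will be performed".

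The Sample size section uses the same undivided level: "A sample size of 88 will be required with 80% power and a 5% (2-sided) significance level".

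**The concern.** The Mann–Whitney test compares two samples. Applied to three arms it can only be run on the three pairs, or after arms are pooled, and the article mentions no pooling. No three-group rank test is named for the primary outcome. The two primary scales then double the number of comparisons, and Fisher's test adds more on the same 6-month outcome.

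The Background and Discussion give the aim as finding the optimal time to operate, and the Abstract says the results will direct surgical decisions. A claim about the best of three timings depends on pairwise differences, and those are the comparisons left without error control. If GOSE and mRS disagree, or the rank test and Fisher's test disagree, the article does not say which result the trial stands on.

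**Working it through.** **Inputs from the article.** Three arms, hence 3 pairs. Two primary scales. A two-sample test. Two-sided level 0.05, stated once and not divided. Total 99, taken as 33 per arm (equal allocation assumed).

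**Inputs assumed.** Each test is run at 0.05, as follows from the single stated level. The between-scale correlation ρ is not in the article and is varied. All figures are under the global null, that is, no difference between any timings.

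**Step 1: the stated figure.** One two-sample test on one scale at 0.05 has a 5% error. Simulated with ordinal scales at 29 per arm, a single pair gives 4.5–5.1%. So the 5% is right for one comparison.

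**Step 2: one scale, three pairs.** With equal arms, each pairwise statistic is |zᵢ − zⱼ|/√2. At least one pair is significant when the range of three standard normals exceeds 1.96 × √2 = 2.772. For three groups that probability is 12.2%. It is below the independence value 1 − 0.95³ = 14.3% because the three pairs share arms. A simulation of 1,000,000 runs gives 12.2–12.3%, and Mann–Whitney tests on simulated ordinal scales at 33 per arm give 12.0–12.5%.

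**Step 3: two scales, a significant pair on either counts.**

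| ρ (assumed) | Chance of at least one false significant pair |
|---|---|
| 0 | 22.9% |
| 0.7 | 19.6% |
| 0.8 | 18.4% |
| 0.9 | 16.7% |
| 0.95 | 15.5% |
| 1 | 12.2% |

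Six independent tests would give 1 − 0.95⁶ = 26.5%. Over the whole range of non-negative ρ, the rate does not fall below 12.2%. Ordinal-scale simulation at 33 per arm agrees: 15–21% for latent correlations of 0.98 down to 0.6.

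**Step 4: Fisher tests, if also pairwise.** Counting these as further routes to a positive result raises the rate to 19–25% over the same latent correlations. On one scale alone, Mann–Whitney plus pairwise Fisher gives about 15%.

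**Step 5: rules the article does not state.** Requiring both scales to be significant on the same pair gives 4.4–9.0% (ρ 0.7–0.95). A three-group test first on each scale, with either scale sufficing, gives 8.4–6.6% over the same ρ.

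**Step 6: the proposed procedure.** One primary scale with a three-group test at 5% before the pairs gives 4.6–5.3% in ordinal simulation at 29 per arm. With exactly three groups this holds in general. If all arms are equal, the overall test limits the error to 5%. If they are not all equal, at most one pairwise null can be true, and it is tested at 5%.

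**The case against.** Five points can be made for the plan as it stands.

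- **A statistical analysis plan may exist.** Testing order and multiplicity rules are commonly left to it. That is fair for those details. But the two-sample test and the two unranked primaries are chosen in the article itself, and a later document could cure the problem only by overriding them.
- **The 5% is a significance level.** The article never calls it a family-wise rate. That stands: the article does not make a false statement about the family-wise rate. The plan simply leaves that rate uncontrolled.
- **Fisher's test may be a single test.** It extends to three-group tables, and the article does not say it is pairwise or applied to a dichotomy of each scale. A reader might infer 12 primary tests (3 pairs × 2 scales × 2 tests), but the text does not fix that number. The Fisher sentence can even be read as handing the significance decision to Fisher's test. That reading is possible, but the wording is ambiguous and does not establish it.
- **The size depends on correlation.** A reader might quote 18–20% as the trial's error rate. With Mann–Whitney tests alone that needs ρ of about 0.7–0.8, which the article does not supply. Only the 12% for one scale is free of this assumption.
- **A false difference is not a false optimum.** A reader might infer that one null trial in five would name a best timing. The documents do not support this. If optimal means significantly better than both other arms, the null rate is about 1.4% on one scale and 1.9–2.5% with either scale (ρ 0.95–0.7, Fisher not counted). The article states no rule for declaring an optimum, so the larger rates apply to at least one false significant difference and nothing more.

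**Conclusion.** The point holds as wrong as written. Three arms, a two-sample test for the 6-month outcome, two primary scales without priority and one undivided 5% level are all in the text. Following it means ungated pairwise testing.

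The chance of at least one false significant difference is about 12% on a single scale. With both scales it is roughly 15–20%, on three assumptions: a between-scale correlation of 0.7–0.95, any one pair on either scale counting, and no overall test first. It is higher if pairwise Fisher tests count as well. The need for the change does not depend on where in that range the true figure lies.

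**What to change.** Before analysis, amend the Follow-up and Statistical analysis sections as follows.

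1. Designate one of GOSE and mRS at 6 months as the primary outcome and the other as secondary. The article gives no ground for preferring either, so the choice is the sponsor's.
2. Test the primary scale with one three-group test at two-sided 5%: Kruskal–Wallis, or a 2-degree-of-freedom test from an ordinal model.
3. Make the three pairwise Mann–Whitney comparisons, each at 5%, only if that test is significant.
4. Make the Fisher comparison of unfavorable outcome secondary.

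The cost is analysis wording, with no extra patients. One scale loses primary status, and no pairwise claim can be made without a significant overall test.

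A Bonferroni division would also control the error, at 4.4% for one scale at 0.05/3 and 3.1–4.5% for both at 0.05/6, but it costs power. For unfavorable outcome of 50% versus 20% at 33 per arm, the power of one pairwise comparison of proportions falls from 73% at 0.05 to 57% at 0.05/3 and 47% at 0.05/6.
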